## Abstract

**Background:**

Mechanical neck pain is a highly prevalent problem in primary healthcare settings. Many of these patients have restricted mobility of the cervical spine. Several manual techniques have been recommended for restoring cervical mobility, but their effectiveness in these patients is unknown. The aim of the present study is to compare the effectiveness of two types of specific techniques of the upper neck region: the pressure maintained suboccipital inhibition technique (PMSIT) and the translatory dorsal glide mobilization (TDGM) C0-C1 technique, as adjuncts to a protocolized physiotherapy treatment of the neck region in subjects with chronic mechanical neck pain and rotation deficit in the upper cervical spine.

**Methods:**

A randomized, prospective, double-blind (patient and evaluator) clinical trial. The participants (*n* = 78) will be randomly distributed into three groups. The Control Group will receive a protocolized treatment for 3 weeks, the Mobilization Group will receive the same protocolized treatment and 6 sessions (2 per week) of the TDGM C0-C1 technique, and the Pressure Group will receive the same protocolized treatment and 6 sessions (2 per week) of the PMSIT technique. The intensity of pain (VAS), neck disability (NDI), the cervical range of motion (CROM), headache intensity (HIT-6) and the rating of clinical change (GROC scale) will be measured. The measurements will be performed at baseline, post-treatment and 3 months after the end of treatment, by the same physiotherapist blinded to the group assigned to the subject.

**Discussion:**

We believe that an approach including manual treatment to upper cervical dysfunction will be more effective in these patients. Furthermore, the PMSIT technique acts mostly on the musculature, while the TDGM technique acts on the joint. We expect to clarify which component is more effective in improving the upper cervical mobility.

**Trial registration:**

ClinicalTrials.gov NCT02832232. Registered on July 13th, 2016.

## Background

Most cases of pain in the neck region are of mechanical origin [1]. The annual incidence of episodes of mechanical neck pain is estimated at 12 per 1.000 subjects with a primary care medical appointment [2], making it one of the main health problems seen by physiotherapy units in primary care [3]. Its annual prevalence has been estimated as ranging between 16.7% and 75.1% [4]. An annual prevalence of 19.5% has been calculated in the Spanish population [5]. It lasts for 6 months or longer in 14% of cases [6], leading to difficulties not only at work but also in everyday life, at home and in leisure activities [7]. The healthcare costs generated are high, mostly as a result of compensation for sick leave [8, 9].

The most common symptom is pain in the neck region, which may be associated with dizziness, light-headedness, restricted movement [10] and manifestations of stress [11]. A large proportion of the movement of the cervical spine takes place in the C1-C2 segment, where up to 50% of the total rotation of the cervical spine occurs [12].

There are several techniques to restore cervical mobility, but few of them comply with the guidelines of the IFOMPT (International Federation of Orthopaedic Manipulative Physical Therapists) on safety and effectiveness in treatment of hypomobility of the upper cervical spine, avoiding positions at the end of the range of cervical movement, especially in rotation and extension [13], and there is limited scientific evidence for their effectiveness. The pressure maintained suboccipital inhibition technique (PMSIT) [14] and the translatory dorsal glide mobilization technique in grade III of the atlanto-occipital joint (TDGM C0-C1) described by Olaf Evjenth [15] comply with these recommendations and have been used in previous studies [16], although there is no evidence for their effects on the range of mobility in patients with chronic mechanical neck pain.

Our objective is to compare the effectiveness of the pressure maintained suboccipital inhibition technique and the translatory dorsal glide mobilization technique in grade III of the atlanto-occipital joint as adjunct treatments for physiotherapy in subjects with chronic mechanical neck pain and rotation deficit in the upper cervical spine.

## Methods

### Study design

A randomized, prospective, double-blind (patient and evaluator) clinical trial. The therapist cannot be blinded due to the use of manual techniques. Figure 1 shows a diagram with the different phases of the study.

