### Study population. Sample recruitment

The subjects for this study will be recruited in the Sant Ildefons Rehabilitation Service in Cornellà de Llobregat (Barcelona), a public Primary Care centre of the Catalan Institut of Health. All patients referred to this service must be seen by a specialist in Physical Medicine and Rehabilitation before receiving treatment. All those diagnosed with chronic mechanical neck pain (of more than 3 months duration) and classified in Grade I or Grade II according to the classification of the Neck Pain Task Force [19] during that appointment will be referred to a physiotherapist, who will check whether they meet the other inclusion and exclusion criteria before offering them the opportunity to participate in the study.

The inclusion criteria will be: subjects diagnosed with chronic mechanical neck pain, who are over 18 years old and with a positive result in the flexion-rotation test corresponding to a rotation deficit. The flexion-rotation test (FRT) will be considered as positive if in a position of maximum cervical flexion, there is a difference of 10 degrees or more in the rotation in one direction compared to the contralateral direction, or if there is a cervical rotation of less than 32 degrees measured with the CROM [12, 20].

The exclusion criteria will be: contraindication to manual therapy, post-traumatic neck pain or red flags according to Rushton et al. [13], an inability to maintain the supine position, use of pacemakers, an inability to perform the FRT, language difficulties that hinder understanding of informed consent or completion of the questionnaires necessary for this study, and subjects with litigation or lawsuits pending.

Patients who meet all inclusion criteria and none of the exclusion criteria will be offered the opportunity to participate in the study and provided with all the relevant information verbally and in writing. They will be told that they will be randomly distributed among the study groups and that each group will be treated with different techniques, all of which are appropriate for their condition, and that the objective of the study is to determine which technique produces the best results. The patients will not be informed about which group they have been assigned to in order to maintain blinding in this regard.

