### Variables studied

The physiotherapist responsible for recruitment (Master’s Degree in Orthopaedic Manual Therapy and 7 years of experience in this field) will perform all the evaluations for this study, and will remain blinded as regards the group that the subject has been assigned to at all times.

Table 1 shows the sociodemographic variables and the values that each one may have. The following variables: age, sex, duration of symptoms, work, work with lifting, work with sustained focal distance, housework, use of mouthguard, presence of dental prosthesis, visual problems, presence and frequency of headaches and analgesic and anti-inflammatory medication will be recorded at the beginning of treatment by anamnesis.

**Table 1 Tab1:** Independent sociodemographic variables

Variable	Values
Age	Years
Sex	Man/Woman
Duration of symptoms	Months
Work	Employed/Unemployed
Work with lifting	Yes/No/Varied
Work with sustained focal distance	Hours
Housework	Hours
Mouthguard	Yes/No
Dental prosthesis	Yes/No
Visual problems	Yes/No
Headaches	Yes/No
Headache frequency	Daily - Weekly - Monthly - Quarterly - Annual
Medication	Yes/No

Table 2 shows the outcome variables, the evaluation period for each one and the measuring instrument used. All evaluations will be performed by a single physiotherapist, who will also be responsible for the recruitment, and who will be blinded throughout the evaluation period as regards the group assigned to each subject.

**Table 2 Tab2:** Outcome variables

Outcome variables	Evaluation period			Measuring instrument
	Baseline	Post-treatment	Three months post-treatment	
Intensity of neck pain (main outome)	X	X	X	VAS
Neck disability	X	X	X	NDI
Overall cervical range of motion	X	X	X	CROM
Upper cervical range of motion	X	X	X	CROM
Headache intensity	X	X	X	HIT-6
Rating of clinical change		X	X	GROC scale

Main outcome will be the intensity of pain in the cervical region measured with a visual analog scale (VAS) from 0 to 100 mm in length, with the extremes defined as “no pain” (0) and “the worst pain imaginable” (100) and without any intermediate points. The test-retest reliability has proven to be good (ICC 0.92) [21].

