#### Control group procedure

The Control Group will only receive the protocolized intervention in 15 daily sessions (Monday through Friday) for 3 weeks. Each session consists of the application of surface thermotherapy (20′ of infrared), an educational discussion (10′ of education about the disease and movement management in the initial sessions, and to answer new questions raised by the patients in subsequently sessions) and kinesitherapy under the physiotherapist’s supervision (30′ of self-stretching of cervical muscles and dorsal flexibility exercises). At the end of the 3 weeks of treatment, patients are instructed to perform self-stretching and dorsal flexibility exercises at home until the final evaluation at 3 months.

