#### Mobilization group procedure

The Mobilization Group will receive the same protocolized treatment and the same instructions as the Control Group, and will also receive 6 sessions (two sessions per week on alternate days) of the translatory dorsal glide mobilization technique (TDGM C0-C1). The technique will be applied for 5 min per session in consecutive cycles of dorsal pushes for about 15 s resting for about 3-5 s, until the first marked resistance felt by the therapist has been exceeded, which would be equivalent to grade III according to the Kaltenborn’s diagram of degrees of movement [34]. Usually this technique is not painful, nevertheless when patient refers pain, pressure is adjusted until a non painful sensation.

The subject will be in supine position and the physiotherapist will position the proximal hand, taking the patient’s occipital in the palm, and the other hand under the posterior arch of the atlas, keeping the fingers extended for greater stability. With the proximal hand, the physiotherapist will position the head in a slight ventral flexion, a slight contralateral tilt and ipsilateral rotation towards the hypomobile atlanto-occipital joint, and will exert pressure with the shoulder on the patient’s forehead in a dorsal direction so that the occipital condyle slides dorsally on the atlas, which remains stable due to being supported in the distal hand (Fig. 2).

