#### Pressure group procedure

The Pressure Group will receive the same protocolized treatment and the same instructions as the Control Group and will also receive 6 sessions (two sessions per week on alternate days) of the pressure maintained suboccipital inhibition technique (PMSIT) [14, 16] applied for 5 min.

The subject will be in supine position and the physiotherapist will be seated at the head of the patient with the forearms resting on the table. The physiotherapist locates the suboccipital region, and applies pressure in a ventral direction in that region by flexing the metacarpophalangeal joints at 90° from fingers III-IV, while the rest of the patient head reposes on the palms of the hands, enabling the pressure to be regulated as perceived by the therapist while performing the technique (Fig. 3).

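### The patient-blind label is not supported for the two technique-versus-control comparisons, where the main outcome is patient-rated

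*Protocol article*

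**What the plan says.** The Abstract (Methods) and the Study design section both claim blinding of patient and evaluator. The latter reads "A randomized, prospective, double-blind (patient and evaluator) clinical trial" and continues "The therapist cannot be blinded due to the use of manual techniques".

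The means of masking patients are given under Study population. Sample recruitment: "The patients will not be informed about which group they have been assigned to in order to maintain blinding in this regard". The same section has patients told that "each group will be treated with different techniques, all of which are appropriate for their condition", and that the study seeks the one with the best results.

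The content of the arms is stated in full. For controls: "The Control Group will only receive the protocolized intervention in 15 daily sessions (Monday through Friday) for 3 weeks", made up of infrared, education and supervised stretching and flexibility exercises. The Mobilization Group gets the same programme and "will also receive 6 sessions (two sessions per week on alternate days) of the translatory dorsal glide mobilization technique (TDGM C0-C1"). The Pressure Group gets the same programme and "will also receive 6 sessions (two sessions per week on alternate days) of the pressure maintained suboccipital inhibition technique (PMSIT"). Each technique is applied for 5 minutes.

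Under Variables studied: "Main outcome will be the intensity of pain in the cervical region measured with a visual analog scale (VAS").

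**The concern.** Withholding a group name conceals the label, not the treatment. A patient whose head and upper neck are held and pressed by a therapist on six occasions knows that it happened, and a patient who only has infrared, education and exercise knows that it did not. The article gives manual treatment as the reason the therapist cannot be blinded. Whether such treatment took place is just as evident to the person receiving it.

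The comparisons with control matter to the trial's conclusions. The Abstract's Discussion predicts that including manual treatment will do better, the Statistical analysis section tests differences across all three groups, and the closing Discussion says positive results would allow the techniques to be recommended for treatment protocols. Whether to add a technique to the standard programme is a technique-versus-control question. On a self-rated outcome, that contrast combines any effect of the specific technique with the effects of being handled and of expecting benefit. Presented under a double-blind label, it would look better protected than it is.

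**Working it through.** **1. What each pair of groups can tell apart**

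| Comparison | Manual technique received | Add-on contact | Is patient masking credible? |
|---|---|---|---|
| Mobilization v Control | yes v no | 30 v 0 min | Not supported by the procedures described |
| Pressure v Control | yes v no | 30 v 0 min | Not supported by the procedures described |
| Mobilization v Pressure | yes v yes | 30 v 30 min | Yes: same number and length of sessions, group not named |

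Two of the three pairwise comparisons are affected.

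**2. Scheduled contact**

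- Common programme (Control group procedure): 20 + 10 + 30 = 60 min per session; 15 × 60 = 900 min.
- Add-on (Mobilization and Pressure group procedures): 6 × 5 = 30 min.
- Totals: 930 v 900 min; 30/900 = 3.3%.

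The amount of attention hardly differs. What differs is its kind: hands-on neck treatment or none.

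**3. Which outcomes the blinded evaluator protects (Table 2)**

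- Patient-rated: VAS (main outcome), NDI, HIT-6, GROC. That is four of six, and blinding the person who collects the form does not mask the person who fills it in.
- Measured by the evaluator with the CROM device: overall and upper cervical range of motion. These are better protected, though not fully: the flexion-rotation test also stops when the patient presents symptoms.

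**4. Size of the bias**

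The document gives nothing from which a bias could be estimated, and this point has no stated figure to reproduce. As an illustration only, suppose there is no true effect and patients' ratings are shifted by b standard deviations in favour of the manual arm. With n per group, the standard error in SD units is √(2/n), and

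P(reject) = Φ(b/se − z) + Φ(−b/se − z).

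The Sample size calculation section gives 26 per group with 15% loss, so about 26 × 0.85 = 22.1, or 22 evaluable, and se = √(2/22) = 0.302. For b = 0.3: 0.3/0.302 = 0.995, and Φ(−0.965) + Φ(−2.955) ≈ 0.169.

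| Assumed b (SD) | n = 22, two-sided 0.05 | n = 22, 0.05/3 | n = 26, two-sided 0.05 | n = 26, 0.05/3 |
|---|---|---|---|---|
| 0 | 5.0% | 1.7% | 5.0% | 1.7% |
| 0.2 | 10.2% | 4.3% | 11.1% | 4.8% |
| 0.3 | 16.9% | 8.1% | 19.1% | 9.5% |
| 0.5 | 38.2% | 23.1% | 43.8% | 27.7% |

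The 0.05/3 columns correspond to the planned Bonferroni post hoc comparisons. The n = 26 columns apply if carrying the last observation forward keeps everyone in the analysis. Every non-zero b is an assumption and none is evidence about this trial. The table shows only that a modest shift in self-rating would matter at this sample size.

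**The case against.** A reader might infer that the control comparisons are effectively unblinded, that they can support no claim about a technique, or that the trial needs a sham arm. The documents do not go that far.

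- **Knowing what one received is not knowing which arm it is.** Patients are told that every group's treatment suits their condition. The article does not describe telling them that any group is a control. Controls get an active programme of 15 one-hour sessions, which the Discussion identifies as the service's own policy, and some may well take it for one of the techniques under comparison. What patients learn about the other arms depends on verbal and written information that is not at hand. This stands: masking is not assured, but its complete failure is not shown.
- **The objective is the comparison of the two techniques.** The Background states it that way, and there the label is credible. This also stands, but the label is applied to the whole trial and the article also draws on the control contrasts.
- **The effect of adding a technique, contact included, is a legitimate adjunct question.** Agreed. The second manual arm also helps: if one technique were better than the other at equal contact, contact alone could not explain it. That inference has to come from the direct Mobilization v Pressure contrast, not from one technique being significant against control and the other not.
- **An article condenses the full protocol.** This does not answer the point. The article states the label, the means of masking and the content of each arm, and these do not agree.

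**Conclusion.** The point holds as a mismatch between the stated blinding and the described procedures, limited to the two technique-versus-control comparisons and weightiest for the four patient-rated outcomes, including the main one. It rests on the arm descriptions being complete, that is, on controls receiving no manual or sham procedure, and on patients being able to perceive a hands-on neck technique. It does not rest on the contact-time gap, which is only 3.3%, nor on the assumed bias values above. The direction of any bias would plausibly favour the manual arms, but its size is unknown. The design itself is sound for an adjunct question. What needs correcting is the label and the strength of claim attached to the control contrasts.

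**What to change.** 1. In the Abstract and the Study design section, describe the trial as evaluator-blinded, with patients masked to group name and patient masking credible only between the Mobilization and Pressure Groups.
2. Identify Mobilization v Pressure as the masked, contact-matched comparison that answers the stated objective.
3. In the Statistical analysis section and the Discussion, state that contrasts with control on VAS, NDI, HIT-6 and GROC estimate the effect of adding the technique, including its manual contact and the expectation that goes with it, and will not be presented as double-blind evidence of a technique-specific effect.
4. Optionally, ask each patient at the end of treatment which group they believe they were in, and report the answers by arm. This would show how far withholding the group name worked.

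The cost is a few sentences, a weaker claim against control and, if item 4 is adopted, one extra question. No arm, treatment or sample size changes, and no sham is required.

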**Fig. 1 Fig1:**
[figure not shown]
Consort Diagram: Flow of the participants throughout the study

### Sample size calculation

The required calculation of the sample size was performed for all outcome variables, for a two-tail test, using a web application (Granmo v7.12) from the Mar Institute of Medical Research Foundation (https://www.imim.es/ofertadeserveis/software-public/granmo/). The statistics needed for the calculation were determined based on three studies: the pilot study by González-Rueda et al. [16] provided statistical data about pain intensity in a similar population and with similar techniques to those used in this study, and those by Izquierdo et al. [17] and Dunning et al. [18] comparing different manual techniques in patients with chronic mechanical neck pain provided statistical data about Neck Disability Index (NDI), range of active mobility an Headache Impact Test. The highest value obtained, using an alpha risk of 0.05 and a beta risk of 0.20 with an estimated follow-up loss of 15%, was 26 subjects per group. As there will be three study groups (the Control Group, the Mobilization Group and the Pressure Group) the total sample size will be 78 subjects.

### Study population. Sample recruitment

The subjects for this study will be recruited in the Sant Ildefons Rehabilitation Service in Cornellà de Llobregat (Barcelona), a public Primary Care centre of the Catalan Institut of Health. All patients referred to this service must be seen by a specialist in Physical Medicine and Rehabilitation before receiving treatment. All those diagnosed with chronic mechanical neck pain (of more than 3 months duration) and classified in Grade I or Grade II according to the classification of the Neck Pain Task Force [19] during that appointment will be referred to a physiotherapist, who will check whether they meet the other inclusion and exclusion criteria before offering them the opportunity to participate in the study.

The inclusion criteria will be: subjects diagnosed with chronic mechanical neck pain, who are over 18 years old and with a positive result in the flexion-rotation test corresponding to a rotation deficit. The flexion-rotation test (FRT) will be considered as positive if in a position of maximum cervical flexion, there is a difference of 10 degrees or more in the rotation in one direction compared to the contralateral direction, or if there is a cervical rotation of less than 32 degrees measured with the CROM [12, 20].

The exclusion criteria will be: contraindication to manual therapy, post-traumatic neck pain or red flags according to Rushton et al. [13], an inability to maintain the supine position, use of pacemakers, an inability to perform the FRT, language difficulties that hinder understanding of informed consent or completion of the questionnaires necessary for this study, and subjects with litigation or lawsuits pending.

Patients who meet all inclusion criteria and none of the exclusion criteria will be offered the opportunity to participate in the study and provided with all the relevant information verbally and in writing. They will be told that they will be randomly distributed among the study groups and that each group will be treated with different techniques, all of which are appropriate for their condition, and that the objective of the study is to determine which technique produces the best results. The patients will not be informed about which group they have been assigned to in order to maintain blinding in this regard.

If they decide to participate they will be asked to sign an informed consent form and the same physiotherapist responsible for recruitment will perform the baseline assessment.

